The combined use of SBP and exercise rehabilitation offers synergistic benefits, particularly in improving myocardial blood supply. SBP promotes angiogenesis, increasing coronary microvessel number and diameter, while exercise rehabilitation enhances collateral circulation, boosting blood perfusion efficiency in both new and existing microvessels. This integrated approach is more effective in mitigating myocardial ischemia. We suggest that synchronizing SBP with exercise rehabilitation enhances therapeutic outcomes through three aspects: (1) improved coronary microcirculatory function; (2) reduced major adverse cardiovascular events within a year; and (3) enhanced patient quality of life. This study introduces an integrative model for post-PCI microvascular rehabilitation, merging traditional Chinese medicine’s systemic regulation with Western exercise physiology’s biomechanical precision, marking a shift from fragmented approaches. Successful validation could reshape international guidelines, providing the first Class I recommendation for combined pharmaco-mechanical CMVD management.

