### Data collection and outcome measures

2.4

Eligible patients will be informed of the trial, agree to participate, and voluntarily sign the informed consent form. At the first visit, clinicians will collect basic clinical data of patients, including gender, age, medical history, and medication history. The next day, special personnel will measure patients’ height, weight, waist circumference, and resting blood pressure, and collect fasting venous blood for biochemical tests. In the data collection process, participants are assigned ID numbers, which are used as their identifiers in the system to safeguard their real identities. The collected information is stored in a highly secure database with strict access control, accessible only to the study leader and statistical experts. This ensures effective protection of participants’ privacy throughout the trial. Details of the outcome measures are shown in Table 7.

**Table 7 tab7:** Details of the outcome measures.

Outcome type	Specific content	Evaluation time	Evaluation method
Primary outcome	Evaluation of coronary microcirculation	Immediately and 1 year after revascularization	Myocardial contrast echocardiography (MCE): MBF; myocardial perfusion imaging (MPI): SDS
Secondary outcomes	Incidence of angina pectoris	1 month, 3 months, 6 months, and 12 months after revascularization	Clinical observation and recording
Secondary outcomes	Incidence of MACE during hospitalization, including all-cause death, recurrent myocardial infarction, and target lesion revascularization	Period of hospitalisation after revascularisation	Clinical observation and recording
Secondary outcomes	Incidence of 1-year MACE, including all-cause death, recurrent myocardial infarction, and target lesion revascularization	1 year after revascularization	Clinical observation and recording
Secondary outcomes	Assessment of quality of life improvement using SAQ	Period of outpatient review after discharge	Scoring with the validated Chinese version of the SAQ
Secondary outcomes	Inflammatory factors, angiogenesis-related factors, exercise-related factors	1 month, 3 months, 6 months, and 12 months after revascularization	Biochemical tests: IL-1, IL-6, and TNF; VEGF, Ang, NO, and eNOS; FSTL1 and FGF 21

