### Statistical analysis

2.9

In this study, there is currently insufficient reference data based on the primary outcome to support sample size calculations; therefore, pilot studies are being conducted to obtain the key parameters required for the formula:

$$n=\varphi^{2}(\sum S_{i}^{2}/g)/[\sum {\left({\bar{X}}_{i}-\bar{X}\right)}^{2}/(g-1)]$$

(where the formula parameter *g* = 4, representing a total of 4 groups in the study) to estimate the required sample size scientifically and accurately, with the significance level set as two-tailed *α* = 0.05, the statistical power set as 1-*β* = 90% (*β* = 0.1), and after calculating the theoretical sample size for each group using the formula upon completion of the pilot studies, a 20% dropout rate will be considered to adjust the theoretical sample size to obtain the final sample size for each group, with the total sample size of the study being the final sample size of each group multiplied by 4.

Statistical analyses will be conducted using appropriate methodologies based on the data characteristics. Continuous variables will be reported as means ± standard deviations, while categorical variables will be presented as frequencies and percentages. Group differences will be assessed using t-tests, analysis of variance (ANOVA), or chi-square tests, as appropriate. A *p*-value of less than 0.05 will be considered indicative of statistical significance. All statistical analyses will be conducted using software such as SPSSAU.

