SBP and exercise rehabilitation interact across multiple physiological action pathways; they all exert positive effects on cardiac function, vascular endothelial function, and hemodynamics. Pharmacokinetic aspects: low-to-moderate-intensity exercise enhances whole-body metabolic status, making the environment conducive to drug metabolism. Particularly in the digestive system, compared to intense exercise, low- to moderate-intensity exercise is beneficial for drug absorption; it allows for faster efficacy and a better degree of absorption (40). Moreover, long-term exercise training also increases the activity of liver enzymes, such as cytochrome P450, which break down medications, lowering the risk of drug buildup in the body (41). The study noted that co-administration of these has a significant impact on enhancing cardiac function and improving the quality of life in patients with cardiovascular diseases (33).

This study has the following advantages: in study design, strict adherence to evidence-based medical norms. The generation of random sequences by computer, and complete distribution concealment with opaque envelope seals, raises the credibility of the study findings. In addition to the primary outcome, the Seattle Angina Questionnaire (SAQ) will also be used to evaluate the quality of life of the patients, to comprehensively reflect the impact of the treatment, on the overall state of the patient from the patient’s subjective feelings, to provide a more thorough viewpoint for evaluating the treatment effect. In addition to routine clinical outcomes, this study will also gather multidimensional data on inflammatory factors, angiogenesis-related and exercise-related factors, digging into the mechanism in detail at the molecular level. Nevertheless, this study also has some limitations. The study was conducted in only one tertiary A hospital; all subjects were recruited from a single source, which may affect the stability and extrapolation of the findings. Moreover, data collection during the trial was made more challenging by the 1-year follow-up period and possible high dropout rate, which will make the study less effective.

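### One-year MACE is left to a comparison of proportions that cannot use partial follow-up; a time-to-first-event analysis would remove a rate error of about 10% if one patient in five were lost.

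*Protocol article*

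**What the plan says.** In the protocol article, Table 7 (section 2.4) lists as a secondary outcome "Incidence of 1-year MACE, including all-cause death, recurrent myocardial infarction, and target lesion revascularization", obtained by clinical observation and recording. The Background gives "reduced major adverse cardiovascular events within a year" as one of the three ways in which the combined treatment should help.

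Section 2.9 states that "categorical variables will be presented as frequencies and percentages" and that "Group differences will be assessed using t-tests, analysis of variance (ANOVA), or chi-square tests, as appropriate". It names no method that handles censored follow-up and no rule for a patient whose MACE status at 1 year is unknown.

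On loss to follow-up, section 2.9 says "a 20% dropout rate will be considered to adjust the theoretical sample size". The Discussion lists as a limitation a "possible high dropout rate, which will make the study less effective".

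**The concern.** Chi-square is the only listed test that suits an incidence. It treats every patient in the denominator as if observed for the full year. A patient who leaves at month 3 without an event must be counted as event-free for nine months that nobody saw, or be removed. If only event-free leavers are removed, patients who had an event before leaving stay in, and the rate rises. The first rule pushes the rate down and the second pushes it up, so the reported 1-year MACE rate depends on a choice that the article does not fix.

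The comparison between arms is at risk only if loss differs by arm or depends on prognosis. Differing loss is plausible here. Participants and treating staff are not blinded (section 2.3). The exercise arms carry outpatient sessions and exercise data upload, while controls receive routine care after PCI (sections 2.3 and 2.5.1). Section 2.3 also allows participants to be excluded if they learn their assignment during rehabilitation exercises, which could remove patients unevenly.

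**Working it through.** The article gives no sample size, MACE rate or timing of loss, so it has no figure of its own to reproduce. The check asks how far each way of forming the proportion departs from the true 1-year risk.

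**Inputs**
- D = 0.20, the share of patients whose MACE status is lost. This borrows the allowance in section 2.9 and is an assumption for MACE.
- p, the true 1-year MACE risk: not given; assumed 5% to 30%.
- Event times: constant hazard λ = -ln(1 - p) per year, so F(t) = 1 - exp(-λt).
- Timing of loss: not given; assumed uniform over the year, or all at a single time between months 1 and 11. Loss is independent of prognosis.

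**Formulas**
- Observed event proportion: E = (1 - D)p + D × mean F(t).
- (a) Lost patients counted as event-free: estimate = E.
- (b) Only event-free leavers dropped: estimate = E / [E + (1 - D)(1 - p)].
- (c) All leavers dropped, including those with an event already seen: estimate = p.

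**Worked case: p = 0.10, uniform loss**
- λ = 0.1054, and mean F(t) = 1 - 0.10/0.1054 = 0.0509.
- E = 0.80 × 0.10 + 0.20 × 0.0509 = 0.0902.
- (a) 0.0902/0.10 = 0.902, an error of -9.8%.
- (b) 0.0902/(0.0902 + 0.72) = 0.1113, an error of +11.3%.
- (c) error 0%.

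**Range with D = 0.20**

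| Timing of loss | p | (a) counted event-free | (b) event-free leavers dropped |
|---|---|---|---|
| Uniform | 5% | -9.9% | +11.9% |
| Uniform | 30% | -9.4% | +8.9% |
| All at month 3 | 10% | -14.8% | +5.8% |
| All at month 9 | 10% | -4.8% | +16.8% |
| Months 1 to 11 | 5-30% | -18.3% to -1.4% | +1.7% to +21.6% |

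With D = 0.10 and uniform loss, the error is about 4-5% in either direction.

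**Comparison between arms, uniform loss**
- Equal 20% loss, no true effect: the risk ratio stays 1.00 and the test size stays 5.0%.
- Equal 20% loss, true risk ratio 0.60 (15% against 9%): estimated as 0.599 under (a) and 0.604 under (b).
- Unequal loss, 10% against 30% (assumed), p = 10% in both arms:
  - E = 0.09 + 0.1 × 0.0509 = 0.0951 and E = 0.07 + 0.3 × 0.0509 = 0.0853.
  - Under (a) the risk ratio is 0.0853/0.0951 = 0.90.
  - Under (b) the rates are 0.0951/(0.0951 + 0.81) = 0.1051 and 0.0853/(0.0853 + 0.63) = 0.1192, a ratio of 1.13.
- Type I error for that unequal case under (a), by normal approximation: 5.3%, 5.7% and 6.4% at 50, 100 and 200 patients per arm (assumed sizes).

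**The case against.** The strongest reply is that the article never assigns chi-square to MACE. It lists three tests for all outcomes and leaves the choice to suitability, and a statistical analysis plan that is not shown may name a survival method. The first part is fair: the link is an inference. But the listed options include no time-to-event method, so suitability can only select chi-square for an incidence. The point is therefore about a stated method that fits poorly, and not only about missing detail.

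A reader might infer that the plan expects one patient in five to have unknown MACE status. The article does not say this. The 20% belongs to a sample-size formula meant for the primary imaging outcome. A patient who misses the 1-year imaging may still have known vital status, infarction and revascularisation history. Table 8 gives the nurses regular follow-up, including weekly calls, over months 1 to 12, although section 2.3.2 describes those calls only under the exercise intervention. This objection stands, so the loss rate has to be stated as an assumption.

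A reader might also infer that any use of a proportion must give a wrong rate. That is not so. Excluding all leavers is unbiased under independent loss, which is the same condition that Kaplan-Meier needs. Its cost is that observed events are discarded and precision falls.

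Finally, the between-arm comparison is hardly touched when loss is equal. This stands as well.

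**Conclusion.** The point holds as an inexpensive improvement to the analysis of a secondary outcome that is also one of the trial's stated hypotheses. If MACE status is lost for about 20% of patients, evenly and independently of prognosis, the absolute 1-year rate is about 10% too low or about 9-12% too high in relative terms, depending on the denominator. Across the other assumed timings and risks the error is about 1% to 22%. It is zero if all leavers are excluded and loss is independent.

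The documents do not support a claim that the MACE comparison is invalid or that false positives are grossly inflated. A biased risk ratio needs loss that differs by arm or depends on prognosis. The 10% against 30% example is invented for illustration, and even there type I error rises only modestly.

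Nor should the point be carried over to angina. Table 7 records angina at 1, 3, 6 and 12 months and does not say that it is accumulated over the year.

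**What to change.** In section 2.9, state that 1-year MACE is analysed as time to first event. Event-free patients are censored at last contact or at 12 months, whichever comes first. Report Kaplan-Meier 1-year risks by arm, and compare arms with a log-rank test or a Cox hazard ratio.

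The change takes a sentence or two in section 2.9. It requires the date of each event and of last contact to be recorded, and needs no extra patients or procedures. The analysis assumes non-informative censoring; if that holds, it recovers the 1-year risk without bias and keeps every observed event. It does not cure loss that depends on prognosis.

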## Abstract

**Background:**

CTO-PCI is generally successful, but 40–55% of patients experience coronary microvascular dysfunction (CMVD) afterward, raising the risk of cardiovascular issues. Shexiang Baoxin Pill (SBP) aids angiogenesis and cardiovascular health, while exercise rehabilitation boosts coronary collateral circulation. However, the combined impact of these treatments on CTO-PCI patients remains under-researched.

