### Study design

2.1

This study is a prospective, single-center, randomized controlled clinical trial. Patients with CTO who underwent PCI in the cardiology department of our hospital. Using a computer-generated block randomization sequence (block size = 4), participants were allocated in a 1:1:1:1 ratio to one of four parallel groups: the SBP group, the exercise rehabilitation group, the combined SBP and exercise rehabilitation group, and the control group. Allocation concealment was ensured by a central randomisation module embedded in the Hospital Information System (HIS); the treatment assignment was automatically released only after the participant had been registered and baseline data entry was completed. Figure 1 shows the details of the study process. This study will strictly adhere to the Standard Protocol Items: Recommendations for Interventional Trials (SPIRIT) reporting standard (20).

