## Conclusion

4

This protocol presents a methodologically robust and innovative approach to addressing post-CTO-PCI microvascular dysfunction through integrative medicine. By combining SBP’s multi-target pharmacology with precision-guided exercise rehabilitation, the study aims to establish a new paradigm for microvascular protection. Its findings may catalyze future research on synergistic therapies and inform global guidelines for high-risk coronary artery disease populations.

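### The planned 90% power belongs to a four-group omnibus test, while the hypothesis is about what the combination adds to its components

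*Protocol article*

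**What the plan says.** **Hypothesis.** Section 1 (Background) states that "The combined use of SBP and exercise rehabilitation offers synergistic benefits, particularly in improving myocardial blood supply" and proposes that giving the two together improves microcirculatory function, one-year MACE and quality of life. The abstract gives as motivation that "the combined impact of these treatments on CTO-PCI patients remains under-researched". Section 4 (Conclusion) looks ahead: "Its findings may catalyze future research on synergistic therapies".

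**Design.** Under section 2.1 participants are "allocated in a 1:1:1:1 ratio to one of four parallel groups": SBP, exercise, both, or control. The article does not use the term, but this is a complete 2x2 factorial layout.

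**Sample size.** Section 2.9 gives n = φ²(ΣSᵢ²/g) / [Σ(X̄ᵢ − X̄)²/(g − 1)] with g = 4, "representing a total of 4 groups in the study", "with the significance level set as two-tailed *α* = 0.05" and "the statistical power set as 1-*β* = 90% (*β* = 0.1)". The means and SDs are to come from pilot studies, a 20% dropout allowance is then added, and no N is stated yet.

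**Analysis.** The same section says: "Group differences will be assessed using t-tests, analysis of variance (ANOVA), or chi-square tests, as appropriate". It names no primary contrast and no interaction term.

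**The concern.** The formula in section 2.9 depends on the four means only through their overall spread. It sizes a test of whether any arm differs from any other. The hypothesis in section 1 needs two more specific answers: whether the combination beats SBP alone and exercise alone, and, for synergy, whether its effect exceeds the sum of the two single effects.

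An N that is right for the first question can be far too small for the others. A significant omnibus result could also come entirely from the gap between treated patients and controls. If N is set this way, a later analysis plan can name the right contrasts but cannot restore the missing power. The trial could then end with a clear difference between arms and no usable evidence on what the combination adds.

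**Working it through.** The article gives no N to reproduce, so the check asks what power its own formula leaves for the contrasts of interest.

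**Inputs from section 2.9:** g = 4, two-sided α = 0.05, power 90%.
**Assumed, because the article gives no values:** a common SD σ, a single-component effect d, and four patterns of means in the order control, SBP, exercise, combined. Results use large-sample normal approximations and do not depend on the size of d.

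**Step 1: what the formula fixes.** Rearranged, it says n·SS/σ² = (g − 1)φ² = λ, where SS = Σ(X̄ᵢ − X̄)². For 3 degrees of freedom, α = 0.05 and 90% power, λ = 14.17, so φ² = 14.17/3 = 4.72 and φ = 2.17. Write k = n·d²/σ² = 14.17/(SS/d²).

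**Step 2: expected z for each contrast at that n.**
- Combined versus one component, true difference Δ·d: z = Δ·√(k/2).
- Interaction (combined − SBP − exercise + control), true value I·d: z = I·√k/2.
- Two-sided power is approximately Φ(z − 1.96).
- Beating both components: joint probability for two z statistics with correlation 0.5, since they share the combined arm.

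**Step 3: numbers.**

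| Means | SS/d² | k | z vs one component | Power vs one | Power vs both | z interaction | Power interaction |
|---|---|---|---|---|---|---|---|
| 0,d,d,2d (additive) | 2 | 7.09 | √3.54 = 1.88 | 47% | 30% | 0 | no synergy |
| 0,d,d,3d (synergy) | 4.75 | 2.98 | 2·√1.49 = 2.44 | 69% | 54% | √2.98/2 = 0.86 | 14% |
| 0,0,0,d (only the combination works) | 0.75 | 18.90 | √9.45 = 3.07 | 87% | 78% | √18.90/2 = 2.17 | 58% |
| 0,d,d,d (combination adds nothing) | 0.75 | 18.90 | 0 | no added benefit | no added benefit | −2.17 | no synergy |

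In every row the omnibus test has 90% power by construction. In the last row it rejects 90% of the time although the combined arm equals each single arm. In the first row, combined versus control has z = 2·1.88 = 3.76 and power 96%. A weaker synergy than those in the table (0,d,d,2.5d) leaves about 8% power for the interaction.

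**Step 4: how much larger n would have to be.** A contrast needs z = 1.96 + 1.28 = 3.24 for 90% power, so n must grow by (3.24/z)².
- Combined versus one component: (3.24/1.88)² ≈ 3.0 times for 0,d,d,2d; (3.24/2.44)² ≈ 1.8 times for 0,d,d,3d; (3.24/3.07)² ≈ 1.1 times for 0,0,0,d.
- Interaction: (3.24/0.86)² ≈ 14 times for 0,d,d,3d; (3.24/2.17)² ≈ 2.2 times for 0,0,0,d.

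As an illustration with d = 0.4 SD and exact noncentral F and t, the additive pattern gives 46 per arm for the omnibus test (58 after 20% dropout). It needs 132 per arm before dropout for one component comparison at 90%.

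**The case against.** Several points on the other side are sound.

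- A reader might infer that the named tests cannot address the combination at all. The text does not support that. A t-test of combined versus SBP, and one of combined versus exercise, would each test superiority over that component. The analysis sentence does not say that the ANOVA is one-way, and a two-way ANOVA contains the interaction. The omnibus reading comes from the sample-size formula alone.
- A reader might also infer that the trial cannot answer its question. That does not follow, because all four cells are randomised and every contrast is estimable. The aim stated at the end of section 3 (Discussion) names no comparator and could be met by combined versus control.
- The synergy statement in section 1 is rationale rather than a formal interaction hypothesis. The abstract speaks only of combined impact, and section 4 refers to future research.
- A condensed article commonly leaves contrasts and model terms to a full protocol or analysis plan, so their absence alone is no fault.
- No N is fixed, so no sample size is yet wrong, and the power figures depend on the assumed pattern of means.
- That a win over usual care would be reported as synergy is a prediction about the authors. The article contains no such rule.

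What remains is the formula. It is stated in the article, it will determine N, and its 90% refers to a test that does not address the hypothesis in section 1.

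**Conclusion.** The point holds as a mismatch between the sample-size target and the hypothesis. The 90% power in section 2.9 does not apply to combined versus each component or to synergy, and the plan neither commits to those contrasts nor powers them. Across the three assumed patterns in which the combination adds benefit, power runs from 47% to 87% against one component and from 30% to 78% for beating both. In the two of those patterns that contain synergy, interaction power is 14% and 58%. None of these reaches 90%, even in the most favourable pattern tried.

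The figures rest on assumed patterns of means, a common SD and large-sample approximations, and the pilot data could point to a different pattern. That the omnibus test can succeed when the combination adds nothing needs no particular effect size. The plan can still be corrected because N is open.

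**What to change.** 1. For the primary outcome, replace the generic analysis sentence with a 2x2 factorial linear model: SBP yes/no, exercise yes/no and their product.
2. Prespecify combined versus SBP and combined versus exercise, as contrasts from that model, as the comparisons that support a claim of added benefit. One workable rule is that both must be significant at two-sided 0.05, which needs no split of alpha between them; other rules are defensible if fixed in advance.
3. Report the interaction contrast with its 95% CI, and make it the only basis for the word synergistic.
4. When the pilot data arrive, apply them to these contrasts and state the power each one has at the chosen N, with the assumed means shown.
5. If the feasible N does not support the component comparisons, limit the stated conclusion to combination versus usual care.

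The cost is a change of wording and a recomputed power statement. The stated power for these contrasts will probably be below 90%. Restoring 90% against one component would take roughly 1.1 to 3 times the omnibus n in the patterns above, and considerably more for the interaction.
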